**Intervention arm**		
Time point	Diet compliance	Exercise compliance
At 3 months	Point of assessment 1	Point of assessment 2
At 6 months	Point of assessment 3	Point of assessment 4
Ovulation induction with letrozole	Yes	Yes
**Control arm**		
At 6 months	Point of assessment 3	Point of assessment 4
Ovulation induction with letrozole	Yes	Yes

For per protocol analysis inclusion only

• Compliance: for a minimum of three points of assessment and at least one ovulation induction cycle with letrozole (intervention arm)

• Compliance: for both the time points (3 and 4) and at least one ovulation induction cycle with letrozole (for control)

Additional analysis (partial compliance)

• Compliance for at least 2 time points of assessment in the intervention (per protocol will include full compliance and those who were partially compliant) and at least one cycle of ovulation induction

• Compliance at least in 1 time point plus at least one cycle of ovulation induction in the control arm

The following will be included in the intention-to-treat analysis only (not included in per protocol or additional analysis)

• Compliance for less than 2 time points irrespective of ovulation induction for intervention

• Compliance for no time points irrespective of ovulation induction for control

• Did not take ovulation induction irrespective of compliance for both the arms

• Who were dropouts (did not turn up at 6 months)

• Did not receive intervention for at least 4 months

Criteria for deciding non-compliance at each visit:

• Diet: participant consuming > 100 cal over the recommended calories intake

• Exercise: participant GPAQ score < 600

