### Dropout criteria

Those participants who are randomized but do not report for further follow-up visits at 3 and 6 months will be considered as dropouts. Randomized participants who withdraw their consent also will be considered as dropouts. The participants who report for the follow-up visit but do not comply with dietary and/or exercise advice will be considered as either non-compliant or partially compliant but will not be considered as “dropouts” as per the agreed criteria shown in Table 1.

**Table 1 Tab1:** Compliance and dropout criteria for inclusion in per-protocol/ITT or additional analysis

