#### Week 26– (session 3) (for both the intervention and control arms)

In person check anthropometry and blood tests (hormones and metabolic parameters) and TVS. The following blood tests will be repeated at 6 months: AMH, serum testosterone, SHBG, serum insulin (fasting and 2 h post-meal), blood sugar (fasting and 2 h post-prandial), fasting lipid profile, glycosylated haemoglobin (HbA1C), SGPT, uric acid and serum adiponectin.

Compliance with dietary intake and physical exercise will be assessed for participants in the intervention and control arms using 24 h diet recall and GPAQ tool.

Medical treatment for infertility can be commenced after 12 weeks on post-randomization in case the participant does not conceive. The lifestyle intervention shall stop at 6 months when a final follow-up on anthropometry, metabolic, hormonal and ultrasound will be done in women from both arms. For those who conceive within 6 months post-randomization, the follow-up will extend until delivery/end of pregnancy for recording obstetrics and neonatal outcomes.

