### Statical analysis

Data will be entered using ICMR software (developed by ICMR, New Delhi) and screened for outliers and extreme values using Box-Cox plot and histogram (for the shape of the distribution). Summary statistics will be used for reporting demographic and clinical characteristics using mean (SD)/median (range) for the continuous variables, and frequency along with percentage for categorical variables. An intention-to-treat analysis and per-protocol analysis for the primary and secondary endpoints will be performed. The continuous endpoints will be tested using *z*-test for means, and the difference in means will be presented with 95% CI. The categorical endpoints will be tested using *z*-test for proportions and the difference in proportion will be presented with 95% CI. A generalized estimating equations (GEE) will be performed to understand the compliance and the effect over time between the two groups of intervention. To understand the advantage of intervention the number needed to treat will be presented.

Based on BMI 23–27 and > 27–35 kg/m^2^, we will perform subgroup analysis to explore whether there is any difference in the effect of the intervention in different subpopulations.

All the randomized subjects will be included in the intention to-treat (ITT) analysis. The ITT analysis is done for the primary endpoint and secondary endpoints and analysed according to the group assigned by randomization. For dropouts with no information on the outcome, it will be assumed that the intervention did not result in a live birth (Table 1).

Per-protocol set (PPS) is the subset of ITT, where the subjects are randomized and treated without any major protocol deviations that impacts the efficacy of the results. The PSS will be used for primary endpoint analysis and secondary end-points. The analysis set will be the subset of participants who are not dropped out of the study and satisfy the protocol requirement. Non-compliant will not be considered for the per-protocol analysis but will be included in the ITT (Table 1). We will perform additional analysis for partially compliant participants and include them in the per-protocol analysis (Table 1). The analysis will be performed by creating an interaction term for the intervention group with partially and fully complaint groups presenting multiple testing-adjusted *p*-values.

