We plan to adjust the results for the following covariates: (i) number of letrozole cycles. Logistic regression analysis will be used to adjust the covariates effectively the adjusted effect size will be presented as an odds ratio (95% CI) for binary outcomes. All the analyses will be performed using STATA/IC 16.0.

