## Discussion

Lifestyle intervention is considered as the first line of management for treating PCOS women who present with infertility. While earlier studies have shown some improvement in menstrual symptoms, endocrinological parameters and ovulation rate, very few have reported clinically important fertility outcomes, i.e. live birth [11–14]. The current trial is planned to capture all the relevant clinical domains which are important to the PCOS women such as reproductive outcomes, improvement in menstrual symptoms, changes in anthropometric measurements and endocrinological parameters and, finally, the quality-of-life score.

High dropout rates and adherence issues are some of the challenges in trials evaluating lifestyle intervention [10, 26]. The Cochrane review evaluating the lifestyle intervention reported high dropout rates (up to 46%), especially in studies involving longer treatment periods [10]. A systematic review investigated the dropout rates in studies evaluating the lifestyle intervention in overweight and obese infertile women [26]. The review included 15 studies, out of which 10 reported the dropout rate. The median dropout rate was 24% (range 0–31%). The authors could not find any modifiable predictors for dropouts and reported lower weight loss in women who had dropped out of the trial. The current study has calculated the sample size taking into account the possibility of high attrition (20%) that may be encountered during the conduct of the trial. In the currently planned trial, it has been hypothesized that customized lifestyle intervention delivered by the medical staff other than the treating clinician may help in greater adherence and lower dropouts. The study will indirectly help us investigate the impact of such an approach on the attrition rate for the lifestyle intervention.

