One of the reasons for planning the current study is the limited applicability of trial findings conducted in other parts of the world, such as Europe and North America due to marked differences in dietary patterns [27]. Furthermore, there are also differences in the level and nature of daily physical activity performed by women from South Asian region versus women from European or North America [28]. Some of the urban areas in South Asia have problems with limited public space and access to sporting facilities. Hence, it is important to customize the lifestyle interventions depending on each individual’s preferences and availability of resources. Moreover, the South Asian phenotype related to obesity is prone to developing complications at a lower body mass index and more resistant to lifestyle intervention [29, 30].

An adequately powered sample size is one of the main strengths of the current study. Involving multiple sites across the different regions of the country will help in the generalizability of the findings. It is hypothesized that the customized lifestyle intervention for PCOS women primarily involving the dietician and physiotherapist and reducing the involvement of medical doctors may help improve compliance. In low-resource settings, the medical doctor is often overburdened and may not be able to deliver such time-consuming interventions in an optimum manner. The intervention, if found to be beneficial, can be replicated in real-world clinical practice, especially in a low-resource setting. One of the limitations of the study is the difficulty in assessing adherence to the given dietary and exercise-related advise. While it is possible to add additional monitoring tools such as electronic gadgets for exercise and measuring diet specific marker or metabolite in blood or urinary sample, we avoided using such tools as it is difficult to replicate such measures in real-world practice, especially in low-resource setting.

Through this protocol, we would like to connect with other investigators who are planning to initiate similar trials or have ongoing projects investigating lifestyle interventions in women with PCOS. We would like to invite the investigators of such projects to join us through a collaborative framework such as prospective meta-analysis or data sharing arrangement plan for future individualized participant metanalysis [31].

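### Table 1 admits controls to the per-protocol set only if they meet 6-month lifestyle cut-offs, so that analysis conditions on behaviour the intervention aims to change; a supportive version based on receipt of allocated care should stand beside it

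*Protocol article*

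**What the plan says.** Table 1 (Dropout criteria) scores diet and exercise at 3 and 6 months in the intervention arm, and at 6 months only in the control arm. Diet fails at more than 100 cal above the recommended intake; exercise fails at a GPAQ score under 600.

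- Per-protocol set, intervention: at least three of four points, plus one letrozole cycle.
- Per-protocol set, control: "Compliance: for both the time points (3 and 4) and at least one ovulation induction cycle with letrozole (for control").
- Partial-compliance analysis, control: "Compliance at least in 1 time point plus at least one cycle of ovulation induction in the control arm".
- Controls who meet neither point are analysed by intention-to-treat (ITT) only.

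The statistical analysis section plans ITT and per-protocol analyses for the primary and secondary endpoints. It describes the per-protocol set as women for whom "the subjects are randomized and treated without any major protocol deviations that impacts the efficacy of the results". On adjustment it says: "We plan to adjust the results for the following covariates: (i) number of letrozole cycles".

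The sections Aim of the study, Control, and Weeks 0 and 1 define the control regimen as usual fertility care with diet and exercise advice given once. The Control section adds that compliance with that advice will not be followed up.

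**The concern.** A control who attended her advice session and took letrozole has had everything her allocation prescribes. If her GPAQ score at 6 months is below 600 she still leaves the per-protocol set, although no deviation in her treatment occurred.

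The arms differ mainly in individualisation and reinforcement: weekly messages, monthly calls and a 3-month visit in the intervention arm only. The purpose is better diet and more activity, and the Discussion expects that "customized lifestyle intervention delivered by the medical staff other than the treating clinician may help in greater adherence and lower dropouts". Restricting both arms to women who reach the cut-offs partly equalises the arms on what the intervention is meant to alter. A benefit seen in ITT could then look weaker per protocol because of how the control set was chosen, and a reader could take this as evidence against the intervention.

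The one named covariate does not help. The number of letrozole cycles arises after randomisation and is cut short by conception, so adjusting for it adjusts for part of the outcome.

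**Working it through.** **Inputs from the article.** Live birth 30% in controls, a 10-point improvement sought, alpha 0.05, power 90%, 473 per arm, 20% attrition (Sample size calculation). No compliance rate is given, nor any share of the effect working through diet and exercise. Those are assumptions below.

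**The plan's own figure.** Two-sided, unpooled variance: (0.30×0.70 + 0.40×0.60) × (1.960 + 1.282)² / 0.10² = 0.45 × 10.51 / 0.01 = 472.8, so 473 per arm. 946 / 0.80 = 1182.5, so 1183. Both reproduce. The design rates are therefore 40% against 30%.

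**Illustration 1: part of the effect works through the cut-offs.** Treat the cut-offs as one target, met by p1 of intervention women and p0 of controls. Let live birth = base + d (if intervention) + m (if target met), in points, with ITT fixed at 40 against 30. If a share s of the 10 points works through the target:

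- m = 10s / (p1 − p0); d = 10(1 − s); base = 30 − p0·m
- Current set, target-meeters in both arms: (base + d + m) − (base + m) = 10(1 − s), whatever p1 and p0
- Added version, target-meeters against all controls: (base + d + m) − 30 = 10(1 − s) + 10s(1 − p0)/(p1 − p0)

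| s | Current set | Added, 75% v 25% | Added, 60% v 40% |
|---|---|---|---|
| 0% | 10 | 10 | 10 |
| 25% | 7.5 | 11.25 | 15 |
| 50% | 5 | 12.5 | 20 |
| 75% | 2.5 | 13.75 | 25 |
| 100% | 0 | 15 | 30 |

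Suppose every woman who would meet the target as a control would also meet it under the intervention. At s = 100% the true effect among women who meet it under the intervention is then 10/0.75 = 13.3 points (75% v 25%) or 10/0.60 = 16.7 points (60% v 40%). Neither version recovers it.

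**Illustration 2: no treatment effect, but women who meet the target have a better prognosis.** Assume live birth of 45%, 35% and 25% in women who would meet the target always, only if supported, or never.

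| Shares always / if supported / never | Intervention target-meeters | Current set | Added version |
|---|---|---|---|
| 0.50 / 0 / 0.50 | 45 | 45 − 45 = 0 | 45 − 35 = +10 |
| 0.40 / 0.20 / 0.40 | (0.40×45 + 0.20×35)/0.60 = 41.7 | 41.7 − 45 = −3.3 | 41.7 − 35 = +6.7 |
| 0.25 / 0.50 / 0.25 | (0.25×45 + 0.50×35)/0.75 = 38.3 | 38.3 − 45 = −6.7 | 38.3 − 35 = +3.3 |

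The overall rate is 35% in both arms in each row.

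**Early conception.** Letrozole starts at 3 months and only in women who have not conceived (Control; Week 26). Conceptions before that count towards the primary outcome. Table 1 sends women without ovulation induction, or with less than 4 months of intervention, to ITT only, and lifestyle advice stops at conception (Safety management). Read literally, the rules can drop women because they conceived. To see the effect, take the last row above and assume that 20% of births among intervention target-meeters are lost this way: (38.3 × 0.80) / (100 − 38.3 × 0.20) = 30.7 / 92.3 = 33.2%. The added difference moves from +3.3 to 33.2 − 35 = −1.8 points; a loss of about 13% brings it to zero.

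**The case against.** Counting adherence to advice as protocol compliance is a defensible choice. Controls are advised too, the Dropout criteria say that women who "do not comply with dietary and/or exercise advice will be considered as either non-compliant or partially compliant" without distinguishing arms, and at week 26 compliance "will be assessed for participants in the intervention and control arms using 24 h diet recall and GPAQ tool". This stands: the rule is not an error, and the current set can be kept.

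The cut-offs are also crude. The intervention also targets refined carbohydrate, sugar, fat, protein and fibre, none of which Table 1 scores, and already active women may pass without changing anything. Only the part of the effect captured by the two cut-offs can be removed, and s = 100% is an extreme. The one-target model also simplifies a rule of three out of four against two out of two.

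The Discussion's remark that "reducing the involvement of medical doctors may help improve compliance" concerns who delivers the advice. Controls also see the dietician and physiotherapist, so that feature is not a contrast between arms. The argument rests instead on individualisation and reinforcement.

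ITT keeps all randomised women as assigned. The planned GEE and the interaction analysis of partial and full compliance would describe differential compliance, but they do not remove the selection: the latter reuses the same sets.

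Finally, comparing intervention women filtered on behaviour with unfiltered controls can favour the intervention. That is true, and is why such an analysis can only be supportive.

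**Conclusion.** The concern holds in a limited form. Table 1 makes control membership of the per-protocol and partial-compliance sets depend on post-randomisation behaviour that the intervention aims to change, although control care does not require it. The part of any effect working through the cut-offs may be removed. In the illustration 10 × (1 − s) points remain, but s is unknown, so the documents fix no size.

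Three stronger readings are not supported. A reader might infer that the trial's main comparison is biased; ITT is untouched. A reader might infer that the per-protocol result must lean towards no difference or towards control, or that the two versions bracket the truth. Those patterns belong to a one-target model, and exclusions linked to early conception can shift them. A reader might also take a version requiring advice plus a letrozole cycle to be controls as allocated; it would still drop controls who conceive in the first 3 months.

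Severity is minor to moderate.

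**What to change.** In Table 1 and the statistical analysis section:

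1. Keep the current per-protocol set.
2. Add one supportive version. A control qualifies by receiving the one-time advice and, only if not pregnant at 3 months, at least one letrozole cycle. For intervention women who conceived before they could meet them, waive the letrozole, 4-month and later compliance-point requirements.
3. Adjust both versions for baseline factors collected in both arms: age, BMI, site, and baseline diet and activity where recorded. Do not adjust for the number of letrozole cycles.
4. Label both versions as supportive to ITT. State that each is selected on post-randomisation behaviour and that neither is unbiased, without asserting a direction.

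The cost is some rewording and one extra analysis, mostly on data already planned (the session 1 food and activity questionnaire, letrozole records, pregnancy status). The downside is that the added version can favour the intervention, because only that arm is filtered on behaviour: +3.3 to +10 points with no true effect in illustration 2. Baseline adjustment may not remove all of that. The change should be made before outcomes are compared by arm.

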
### Safety management and adverse events

Any adverse event (AE), which is any untoward medical occurrence, will be documented by the trial site and periodically reviewed by the trial management team. The serious adverse events (SAEs) will be notified to the sponsor, data monitoring safety committee and other sites by the principal investigators (PI) within a stipulated time period of 48 h.

Any adverse event or reaction which (i) is life or limb-threatening, requires hospitalization or a medical intervention or leads to congenital defect is considered a SAE or serious adverse reaction (SAR).

The following will not be included as AE: (i) medical or surgical procedures during the trial (the condition which led to the procedures is deemed an adverse event), (ii) pre-existing condition which did not worsen during trial period and (iii) other unrelated reason for hospitalization (for example, viral fever or incidental illness).

In the intervention arm, if the participant suffers any fracture or other bodily injury which requires hospital care, then it will be considered a notable event. Any food allergy which leads to a hospital visit or admission should be notified. Overall, the lifestyle advise is considered a low-risk intervention and is very unlikely to give rise to any serious adverse events during the trial period.

The participants who conceive during the trial period will be provided with usual ante-natal care based on local unit protocol. Once the woman conceives, the pre-pregnancy lifestyle intervention advised during the trial will be discontinued and pregnancy-specific advice for diet/physical exercise will be given in both arms.

Early pregnancy complications such as threatened, inevitable, incomplete and complete miscarriage and ectopic pregnancy will be recorded. If they are reported during the trial period, they will be recorded as AE or SAE. However, they will not be considered adverse reaction (AR)/serious adverse reaction (SAR) as the intervention is unlikely to have a causal relationship with the early pregnancy complications. Obstetric complications, namely, pregnancy-induced hypertension, pre-eclampsia and gestational diabetes, will be recorded during the follow-up period. The low birth weight and pre-term birth also will be recorded. Since these outcomes will be observed after the intervention period, they will not be recorded as adverse events.

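### Table 1 drops women who conceive early from the per-protocol and partial-compliance sets, so membership depends on the outcome; the compliance bar also differs by arm

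*Protocol article*

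**What the plan says.** Table 1 lists women who enter the intention-to-treat analysis only and are barred from both the per-protocol and the additional (partial-compliance) analysis. Two entries matter here: "Did not take ovulation induction irrespective of compliance for both the arms" and "Did not receive intervention for at least 4 months". Neither mentions conception.

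Other sections fix when these conditions can be met:

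- Control, and the Week 26 schedule: fertility treatment starts about 3 months (12 weeks) after randomization, and only if the woman has not conceived.
- Safety management and adverse events: "Once the woman conceives, the pre-pregnancy lifestyle intervention advised during the trial will be discontinued". Pregnancy-specific advice then follows in both arms.
- Primary outcome: a live birth counts if conception occurred within 6 months of randomization, with or without letrozole.
- Statistical analysis section: the per-protocol set is used for the primary endpoint and is described as randomized women treated with no major deviation that affects the efficacy result.

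Table 1 also sets the compliance bar. Intervention women have four points (diet and exercise at months 3 and 6) and need three for full compliance or two for partial. Control women have only the two month-6 points and need both, or one for partial. Full and partial compliance also require at least one letrozole cycle in both arms. The analysis section then plans "creating an interaction term for the intervention group with partially and fully complaint groups".

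**The concern.** A woman who conceives in months 0 to 3 cannot take letrozole under the protocol. An intervention-arm woman who conceives before month 4 cannot complete 4 months of the programme. Both followed the plan, and if they deliver, both are primary-outcome successes. Table 1 removes them because they conceived, so membership of the set is partly decided by the endpoint being analysed.

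The trial is open-label and the article itself expects adherence problems, so readers will set the per-protocol result beside intention-to-treat. A disagreement between the two could then be an artefact of the exclusion rule.

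The unequal bar is a separate problem of comparability. The women called fully or partially compliant are defined differently in each arm, and the planned interaction uses those labels.

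**Working it through.** **The plan's own figure.** Inputs from Sample size calculation: 30% vs 40%, alpha 0.05 (two-sided assumed), power 90%. Unpooled formula: n = (1.960 + 1.282)² × (0.3×0.7 + 0.4×0.6) / 0.10² = 472.8, so 473 per arm. With 20% attrition, 946 / 0.8 = 1182.5, so 1183. Both figures reproduce, and the point below does not touch them.

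**Table 1 against the definition.** The analysis section excludes for major deviation. Conceiving before letrozole is due is not a deviation, because letrozole is conditional on not conceiving. Table 1 excludes the woman all the same, so the two passages conflict.

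**Effect of the letrozole rule.** Let L be the true live birth rate, e the share conceiving before letrozole, and s the share of those conceptions ending in live birth. After exclusion the rate is (L − e×s) / (1 − e). The article gives neither e nor s; s = 0.8 is assumed and e is varied.

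| e control / intervention | Control | Intervention | Difference |
|---|---|---|---|
| 5% / 10% | (0.30−0.04)/0.95 = 27.4% | (0.40−0.08)/0.90 = 35.6% | 8.2 points |
| 5% / 15% | 27.4% | (0.40−0.12)/0.85 = 32.9% | 5.6 points |
| 5% / 5% | 27.4% | (0.40−0.04)/0.95 = 37.9% | 10.5 points |
| 10% / 10% | (0.30−0.08)/0.90 = 24.4% | 35.6% | 11.1 points |

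- In the 5% / 10% case, live births removed per 600 women are 600×0.05×0.8 = 24 in control and 600×0.10×0.8 = 48 in intervention.
- With s = 0.7, that case gives (0.40−0.07)/0.90 − (0.30−0.035)/0.95 = 8.8 points. With s = 0.9, it gives (0.40−0.09)/0.90 − (0.30−0.045)/0.95 = 7.6 points.
- With no true effect (30% in both arms), 5% / 10% and s = 0.8: (0.30−0.08)/0.90 − (0.30−0.04)/0.95 = 24.4% − 27.4% = −2.9 points before rounding, a spurious difference.
- Keeping early conceivers in the set leaves the 10 points unchanged in this illustration.

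**Effect of the 4-month rule.** The article does not say how it applies to control women, who receive advice once. Assume e = 5% in both arms and a further 10% conceiving between months 3 and 4. If the rule bites in the intervention arm only: (0.40−0.12)/0.85 − 0.274 = 5.6 points. If it bites in both: 0.329 − (0.30−0.12)/0.85 = 11.8 points.

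**Unequal bar.** Assume every point is passed independently with probability q.

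- Full compliance at q = 0.7: intervention 4×0.7³×0.3 + 0.7⁴ = 65%; control 0.7² = 49%. At q = 0.6: 48% vs 36%.
- Partial or better at q = 0.7: 92% vs 91%. The partial-only group is therefore 91.6 − 65.2 = 26% of intervention women and 91.0 − 49.0 = 42% of control women.
- The full-compliance bar is looser for the intervention arm at any q above 1/3. With perfectly correlated points, both arms qualify at rate q and the gap disappears.

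**The case against.** The strongest reply is about reach. All randomized women are in the intention-to-treat analysis, so every early conceiver's live birth counts there. This is a superiority trial, and the defect is confined to secondary analysis sets. That stands.

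A reader might infer that the rule specifically deletes successes of the intervention. The documents do not support this. The letrozole exclusion applies to both arms. It shrinks the difference only if the intervention yields more conceptions before letrozole. That is a plausible route for the hypothesised benefit, but the article gives no figure for it. With equal early conception the difference widens. The unequal bar does not help this reading either, since above q = 1/3 it is the more lenient one for the intervention arm.

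A reader might also infer that the 10-point difference could vanish. It does so only if the whole gain is assumed to come before letrozole, which makes zero the answer by construction.

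Nor does the article say that women pregnant at month 6 are scored against the withdrawn pre-pregnancy target. The recommended intake could mean the pregnancy advice, and the scoring is simply unstated. If they were scored that way, control would be hit harder, because both its points fall at month 6.

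Finally, control women have no month-3 lifestyle assessment by design, so a four-point bar is impossible for them. That explains the asymmetry but does not make the groups comparable.

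**Conclusion.** The point holds in limited form. Table 1 states, without exemption, a rule that excludes women because they conceived early. It contradicts the article's own definition of the per-protocol set and makes both compliance-based sets depend on the outcome.

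Under the letrozole rule alone, a true 10-point difference would appear as about 5.6 to 8.2 points with early conception of 5% vs 10–15%, or 10.5 to 11.1 points with equal rates of 5–10%. These figures rest on assumed early-conception rates and an assumed 80% live birth share, so neither the direction nor the size is fixed by the documents.

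The different bar is a second, separate defect in comparability: 65% vs 49% at q = 0.7 under independence, and less if points are correlated. Neither defect affects the intention-to-treat result or the sample size.

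**What to change.** Change the analysis wording only:

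1. Reconcile Table 1 with the per-protocol definition: absence of letrozole, or less than 4 months of intervention, is not a reason for exclusion when the reason is conception.
2. Judge compliance in both arms on the assessments due before conception, and state the pass rule when fewer points were due.
3. Add a sensitivity analysis that uses the same month-6 points and the same pass rule in both arms.
4. Name intention-to-treat as the primary analysis. Describe the per-protocol and partial-compliance results, including the interaction, as supportive and open to selection bias, and report by arm how many women were kept without a full compliance test.

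The fourth item is needed because the repair does not remove all selection. Early conceivers have few or no assessments, whereas non-conceivers must pass. In an extreme illustration every conceiver is kept untested, conception equals live birth, and 49% of control and 65% of intervention non-conceivers pass. A true 30% vs 40% then becomes 0.30/(0.30+0.70×0.49) = 46.7% vs 0.40/(0.40+0.60×0.65) = 50.6%, about 4 points.

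The cost is a little more analysis work and a per-protocol set not strictly tested for compliance in early conceivers. No treatment, visit or sample size changes.
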